
Data from demographic and cohort population studies were recently used to provide estimates of overdiagnosis in the service screening setting: in England and Wales, overdiagnosis was estimated to be between 3.3 and 10% of the expected cumulative incidence from age 50 to 79 in the absence of screening after correction for self-selection bias and lead-time bias (Paci et al., 2012 [7]). Evaluation on a large scale is needed to confirm those bias corrections.

Mortality from breast cancer has been declining in the UK population since the early 1990s (CRUK, Accessed 28 March 2013 [1]). This fact coincides with the introduction of both the national screening programme, and new adjuvant therapies, and the respective role of those two factors in mortality reduction is a matter of debate (Cancer Intervention Surveillance Modelling Network (CISNET) Breast Cancer Collaborators, 2006 [8]).

In view of the above, there is a need for a large case–control study to (1) evaluate the effect of the NHSBSP on primary breast cancer mortality, with improvements to design and analysis methodology for coping with bias, notably self-selection bias: we propose to do this by developing a procedure using data from different cancer screening programmes. In addition, there is a need to (2) quantify the relative contributions of screening attendance, tumour attributes and treatment variables on case fatality in primary breast cancer, (3) assess the effect of screening attendance on primary breast cancer incidence, (4) estimate the rate of overdiagnosis due to screening, and (5) estimate the effect of screening attendance on incidence of advanced stage primary breast cancer. This final check may firstly give a result earlier than mortality and therefore confer greater statistical power, and secondly be used as a check on the mortality result. Inconsistency between the observed effect on mortality and that on advanced stage disease will indicate that further work is required to deal with residual bias.

Meeting the above aims will entail retrieving more information than in the traditional case–control evaluation of screening. It will include live incident cases as well as dead ones, and diseased controls as well as disease-free ones. Additional variables such as cancer treatment, breast tumour pathology, and screening attendance at other national screening programmes will also be collected.

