** will be a matched comparison of recently diagnosed/incident invasive and in situ breast cancer cases (C) with the general population controls (D) **free of invasive** and of **invasive or in situ** disease, respectively, with respect to screening exposure strictly prior to the case’s date of **index** diagnosis (set as pseudo-diagnosis date in controls), and will be stratified by age at diagnosis/pseudo-diagnosis. There will be one or two controls per case. This design should allow the evaluation of overdiagnosis due to screening attendance.

**
*Case–control study 4 (CC4)*
** will be a matched comparison of recently diagnosed/incident **advanced stage** breast cancer cases (C) with the general population controls (D) free of advanced stage disease with respect to screening exposure strictly prior to the case’s date of **index** diagnosis (set as pseudo-diagnosis date in controls). There will be one or two controls per case. This design should allow the evaluation of screening attendance on incidence of advanced stage breast cancer. In principle, one should include all advanced breast cancers as cases, i.e. whether advanced at diagnosis or whether subsequently progressed to advanced; however, in practice it will not be possible to identify those that subsequently progress. This analysis will be compared to the analysis of fatal breast cancers to see whether advanced breast cancer can be used as a surrogate endpoint when studying the impact of breast screening on breast cancer mortality.

An overview of the proposed case–control studies and corresponding populations are presented in Figure 1.

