**For CC4**, incident cases (C) will be restricted to those women with advanced stage (defined below) primary breast cancer, and matched general population controls (D) will be restricted to those women who have never had advanced stage primary breast cancer, but may have had in situ or early stage primary breast cancer prior to *and including* the case’s date of index diagnosis. Breast cancer will be defined as “advanced stage” if tumour size is larger than 20 mm, or if at least one regional lymph node is affected, or if both, and as “early stage” if tumour size is equal to or smaller than 20 mm and no regional lymph node is affected. For the purpose of data collection, we have used an inclusive definition of “advanced stage”, but we will also analyse the data by Stage to assess the association between screening and metastatic breast cancer for instance, and using only those cases which are node positive, as this is generally accepted as an important prognostic factor and as a predictor of the effect of screening on mortality (Smith et al., 2004 [10]).

If no matched control is found for a particular case (A or C) with a date of birth within 1 month either side of the case’s date of birth, the range will be expanded to 3 months either side (or 6 months either side if the case’s age at index diagnosis of primary breast cancer is under 50 or over 70).

All cases and controls will appear on the HSCIC database at Exeter. We will aim to select female cases and controls who have been registered with the NHS by age 47 (determined by either date of first registration on local NHAIS system or prior cervical/bowel screening history), and have had available data on both breast and cervical (for women aged 47–64), and, possibly bowel (for women aged 60–69) screening strictly prior to their date of first diagnosis/pseudo-diagnosis (that is, they have been invited to screening at least once), although this may not be practicably feasible for dead cases and matching controls with older age at death. Patient breast, cervical, and bowel (for the main phase) screening history, primary breast tumours attributes and treatment data will be retrieved for all cases and controls, as well as deprivation quintile.

A detailed description of the algorithm to be used for the selection of cases and controls is available from the authors.

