### Study size / Power calculation

The main phase of the study will cover the whole of England with biennial accrual of potentially thousands of cases (circa 18,000 (CRUK, Accessed 28 March 2013 [1])), for which statistical power will not be an issue for any of the case studies, and for which there will be considerable precision. The large sample size will also allow subset evaluation, notably by time since last screen. The sample size for the pilot study was estimated to enable sufficient power to answer the primary objectives addressed by CC1 and CC2 with relative confidence. Results of the pilot with respect to CC3a, CC3b and CC4 objectives will provide the prior estimates currently lacking to perform power calculations.

**CC1.** For the matched comparison of the breast cancer dead cases (A) with the general population controls (B), assuming an odds ratio of 0.7 for the event of ever attending screening (Broeders et al., 2012 [11]), around 900 dead cases and 1800 living controls would confer 90% power to detect such an effect size at the 5% significance level when using a 2-sided test (Machin et al., 1997 [12]).

**CC2.** For the matched comparison of the breast cancer dead cases (A) with the diseased controls (E), no estimate of the odds ratio is available, but it can be assumed to be 0.70 or less for the event of ever attending screening, to be at least consistent with CC1. With only one control per case, 1200 / 900 dead cases and the same number of controls will be required to obtain 90% and 80% power, respectively.

Missing data for some of the breast tumour attributes and treatment can be close to 40-50%, and the pilot sample size will be inflated accordingly. Sensitivity analyses will be conducted for various possible scenarios of non-random missing status.

We are therefore planning to collect pilot data from at least 1400 dead cases (A), together with 2800 general population controls (B) and 1400 diseased controls (E) matched for these. We will also collect at least 1400 recently diagnosed cases (C) and 2800 general population matched controls (D). There will be some degree of overlap between populations (A, C), (C, E) and (B, D).

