**CC2.** The *primary objective* of this case–control will be to estimate the proportional effects of screening attendance *strictly prior to* date of diagnosis/pseudo-diagnosis and cancer treatment, on prognosis in patients diagnosed with primary breast cancer. The primary and secondary measures of attendance to screening will be as for CC1; in addition, they will include tumour detection mode to assess the relationship between detection mode and choice of cancer treatment.

The regression analysis will be adjusted for tumour attributes such as stage of disease at diagnosis and other pathological features. Because of the extreme collinearity between cancer treatment and pathology variables, e.g. lymph node positivity, a major determinant of treatment choice, estimating relative effects from the regression analysis often gives unreliable/biased estimates of cancer treatment (Wishart et al., 2010 [23]). To address this statistical issue, a counterfactual analysis will be performed (Höfler et al., 2005 [24]). The treatment that an individual actually does not receive is called counterfactual treatment, and the outcome under this treatment, after treatment assignment, is referred to as counterfactual outcome. In our study, the cancer treatment effects will be constrained to the absolute effect estimated from meta-analyses of the RCTs.

*Self-selection*, *lead-time, and length* biases will be addressed using the methods described in the *Bias & Effect modification* section. Because in CC2, both cases and controls have had primary breast cancer, *exposure opportunity* bias can be assumed to be minimal.

**
*Secondary objectives*
** will consider time since last screen stratified by epoch of diagnosis to further explore collinearity among the explanatory variables.

**CC3a/b.** The *primary objectives* of these case-controls will be to estimate the effect attendance at breast screening strictly prior to date of diagnosis/pseudo-diagnosis on incidence of invasive (CC3a) or, of in situ and invasive (CC3b) primary breast cancer, and to estimate rates of overdiagnosis due to screening.

The primary and secondary measures of attendance to screening will be as for CC1, in particular time since last screen; in addition, they will include the patient’s age at last screen, and whether a woman ever missed attendance at recall assessment(s). This last measure should help assess potential room for improvement in the management of suspicious screening results.

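### CC2 adjusts for stage and pathology, so its screening coefficient is a direct effect net of stage shift, not screening's contribution to case fatality relative to treatment

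*Protocol article*

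**What the plan says.** The Background section of the protocol article gives the aim behind CC2: to "quantify the relative contributions of screening attendance, tumour attributes and treatment variables on case fatality in primary breast cancer". Under Statistical methods, the CC2 primary objective is "to estimate the proportional effects of screening attendance" and of cancer treatment on prognosis in diagnosed patients. The regression is then described: "The regression analysis will be adjusted for tumour attributes such as stage of disease at diagnosis and other pathological features".

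A counterfactual analysis follows. Its stated reason is a problem with treatment: "Because of the extreme collinearity between cancer treatment and pathology variables, e.g. lymph node positivity, a major determinant of treatment choice", which is said to make regression estimates of treatment effects unreliable. The remedy is also about treatment: "In our study, the cancer treatment effects will be constrained to the absolute effect estimated from meta-analyses of the RCTs".

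Two other places treat stage as a consequence of screening. Under Study design & objectives, CC4 has advanced stage as its outcome ("This design should allow the evaluation of screening attendance on incidence of advanced stage breast cancer"), and its result is to be compared with that for fatal cancers to judge whether advanced disease can act as a surrogate. Under Participants, node positivity is described as accepted "as a predictor of the effect of screening on mortality".

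Under Study size, no odds ratio is available for CC2, "but it can be assumed to be 0.70 or less for the event of ever attending screening, to be at least consistent with CC1".

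**The concern.** A covariate that the exposure changes, and that in turn changes the outcome, is a mediator. Adjusting for it removes from the exposure coefficient the part of the effect that passes through it. By the article's own account, stage and nodal status are such covariates for screening and death from breast cancer. The CC2 screening coefficient is then a direct effect, and the stage shift produced by screening is credited to tumour attributes.

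Treatment is handled differently: its effect is imported from randomised trials and fixed. Setting the two side by side compares screening without one of its main routes of action with treatment at its externally estimated effect. A reader could conclude that screening adds little to case fatality beside treatment when the model had removed screening's part by construction. The Background names the respective roles of screening and adjuvant therapy in the mortality decline as a matter of debate. CC2 is narrower, being about case fatality, but its results will be read in that light.

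**Working it through.** **1. Is stage a mediator in the article's own terms?**

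| Place | Role of stage or nodes |
|---|---|
| CC4, Study design & objectives | outcome of screening; possible surrogate for its mortality effect |
| CC4, Participants | node status predicts the screening effect on mortality |
| CC2, Statistical methods | adjustment covariate beside screening attendance |

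The first two rows place stage between screening and death. The third conditions on it.

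**2. Does the counterfactual step restore the lost part?** It is introduced for collinearity between treatment and pathology, its definitions concern the treatment not received, and its constraint falls on treatment effects. Nothing describes it as recovering the stage-mediated part of screening.

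**3. The plan's own figures.** CC2 states 1200 and 900 pairs for 90% and 80% power at odds ratio 0.70. The control exposure p0 is not given. Case exposure is p1 = 0.70·p0 / (1 − p0 + 0.70·p0). The pooled two-proportion formula (two-sided 5%, as stated for CC1) gives:

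- p0 = 0.86: p1 = 0.602/0.742 = 0.811; 1216 pairs (90%) and 909 (80%). CC1 needs 904 cases, against 900 stated.
- p0 = 0.77 (the coverage quoted for ages 53–70): 855 and 639 pairs; CC1 needs 637 cases.

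The stated sizes therefore match an unstated exposure of about 0.86, and are larger than 0.77 would need. They are not shown to be wrong.

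**4. Attenuation of the screening coefficient.** Let m be the share of the log odds ratio acting through stage and pathology (assumed; no value is given). Taking the split as clean on the log-odds scale, the adjusted odds ratio is 0.70^(1 − m). Power uses the same unmatched formula with 1200 pairs.

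| m | Adjusted OR | Power, p0 = 0.86 | Power, p0 = 0.77 |
|---|---|---|---|
| 0 | 0.70 | 90% | 97% |
| 25% | 0.77 | 66% | 81% |
| 50% | 0.84 | 35% | 47% |
| 75% | 0.91 | 12% | 15% |
| 80% | 0.93 | not computed | not computed |
| 100% | 1.00 | not computed | not computed |

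For example, log 0.70 = −0.357; half is −0.178, and exp(−0.178) = 0.84. These powers ignore the 40–50% missing tumour and treatment data that the article expects, which would lower them further in a complete-case adjusted model.

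**5. Check by simulation.** All inputs are assumed except the 77% screened: advanced stage in 35% of screened and 55% of unscreened women, stage odds ratio for death 4, treatment odds ratio 0.75, treatment given to 70% of advanced and 30% of early cases, one control per case, unmatched logistic regression.

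| Direct screening OR built in | Screening OR, no stage or treatment | Screening OR, adjusted | Treatment OR, adjusted |
|---|---|---|---|
| 1.00 (all through stage) | 0.78 | 1.00 | 0.75 |
| 0.85 | 0.67 | 0.86 | 0.75 |

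Adjustment takes the screening coefficient to its direct effect and leaves the treatment coefficient at its full value.

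**The case against.** The other side has several sound points.

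- **Not the only model.** A reader might infer that CC2 will fit only the adjusted model and so cannot yield screening's overall effect. The text does not go that far. It describes one regression and excludes no other, an article may leave a model sequence to a fuller document, and the CC2 data could give the unadjusted effect because diseased controls are not matched on stage.
- **Tumour attributes are part of the question.** The aim names them as a third contributor, so they belong in a model. That stands. How their share is traced back to screening is not stated.
- **Total benefit comes from elsewhere.** CC1 estimates the effect on mortality with no stage adjustment described, and projected mortality and the prevented fraction draw on CC1 and CC3. A reader might infer that the programme's mortality benefit will be understated; the documents do not support that. But CC1 does not supply a comparison of screening with treatment among diagnosed women.
- **The 0.70 is a planning assumption.** It is borrowed from a study with general-population controls. A diseased-only comparison does not become CC1's total effect when stage is dropped, since lead-time and length bias enter in CC2. It is therefore too strong to say that CC2 has been sized on the wrong quantity.
- **The mediated share is unknown.** That screening will look weak beside treatment is possible, not established.

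None of this changes what the described coefficient measures.

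**Conclusion.** The point holds in this form: the one CC2 regression described conditions on variables that the article treats as affected by screening, so its screening coefficient is a direct effect and does not answer the primary objective when placed beside treatment effects fixed from trials. The counterfactual step is not described as repairing this. The direction follows from the article's own causal account. The size does not: adjusted odds ratios of 0.84, 0.93 and 1.00 rest on assumed mediated shares of 50, 80 and 100% of log(0.70), and the power losses rest also on an assumed exposure prevalence. The adjusted model is legitimate as a direct-effect estimate and should stay, under that label. The change should be made, because a primary objective is affected and the remedy is cheap.

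**What to change.** State three nested CC2 models:

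1. Screening attendance with the planned self-selection, lead-time and length corrections, without tumour attributes or treatment. This is the basis for screening's overall contribution to case fatality.
2. Model 1 plus tumour attributes.
3. Model 2 plus treatment, with the planned constraint to trial estimates.

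Label the screening coefficients in models 2 and 3 as direct effects. Report the change from model 1 to model 2, fitted on the same pairs, as the part acting through tumour attributes, and call it approximate: odds ratios are non-collapsible and some length bias may remain. State that the planning odds ratio of 0.70 applies to model 1, as an assumption taken from CC1, and not to the adjusted models.

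The cost is a change of wording and one or two further models on data already to be collected. Model 1 can also keep pairs with missing pathology. Its drawback is heavier reliance on the lead-time and length corrections, so the planned sensitivity analyses for those should be reported with it.

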## Methods/Design

### Study design & objectives

This study is comprised of two sets of retrospective matched case–control studies: the first set involves dead cases of primary breast cancer (cases A), and the second set, recently diagnosed (or incident) cases of primary breast cancer, dead or alive (Cases C). The dead cases will be matched with two different sets of controls: two general population controls who were alive at the case’s date of death (Controls B), and one diseased control who was alive at the case’s date of death and had had invasive primary breast cancer (screen-detected, interval and never screened will all be included) at the case’s date of first diagnosis (Controls E). The incident cases will be matched to two controls from the general population (Controls D). Subsets of cases and matched controls will be selected for the purpose of each case–control evaluation objective (see *Participants*: *Selection of cases & controls* for details).

**
*Case–control study 1 (CC1)*
** will be a matched comparison of the breast cancer dead cases (A) with the general population controls (B) with respect to screening exposure strictly prior to the case’s date of first diagnosis (set as pseudo-diagnosis date in controls). There will be two controls per case. This design should allow the evaluation of screening exposure modalities in relation to mortality from breast cancer.

**
*Case–control study 2 (CC2)*
** will be a matched comparison of the breast cancer dead cases (A) with the diseased controls (E) with respect to screening exposure strictly prior to the case’s date of first diagnosis (set as pseudo-diagnosis date in controls). There will be one control per case. This design should enable assessment of the interplay between screening attendance, tumour attributes and treatment variables on fatality from breast cancer.

**
*Case–control study 3a (CC3a - Incidence)*
** will be a matched comparison of recently diagnosed/incident **invasive** breast cancer cases (C) with the general population controls (D) free of invasive disease with respect to screening exposure strictly prior to the case’s date of index diagnosis (set as pseudo-diagnosis date in controls). There will be one or two controls per case. This design should allow the evaluation of screening attendance in relation to breast cancer incidence.

**
*Case–control study 3b (CC3b - Overdiagnosis)*

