*Population of cases C-matched general population controls (D)* For each case C, two women will be selected from the general population in the HSCIC database at Exeter who, are registered in the same NHAIS system as the case at the case’s date of index diagnosis, are alive at case’s date of index diagnosis, and were born within 1 month either side of the case’s date of birth. For subsequent phases of this evaluation (main phase onwards), they will not have been included as population controls B, E, or D in previous evaluation periods, although they may be included as controls B or E within the same evaluation period.

Incident cases (C) and matched general population controls (D) will be selected *a posteriori* by the PRU, using tumour information, to suit the purpose of each case-study (see Figure 1).

**For CC3a**, incident cases (C) will be restricted to those women with invasive breast cancer, and matched general population controls (D) will be restricted to those women who have never had invasive primary breast cancer, but may have had in situ primary breast cancer prior to *and including* the case’s date of index diagnosis.

**For CC3b**, all incident cases (C) will be selected. For in situ cases, matched general population controls (D) will be restricted to those women who never had primary breast cancer (in situ or invasive) prior to *and including* the case’s date of index diagnosis; for invasive cases, to those women who never had invasive primary breast cancer, but may have had in situ primary breast cancer.

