### Statistical methods

All case–control study analyses will be conducted using conditional logistic regression. Matching factors (i.e. age, area) are controlled for in the design. All statistical analyses will be performed using the statistical software STATA or R.

**CC1.** The *primary objective* of this case–control will be to assess the effect of various measures of attendance at breast screening *strictly prior to* the case’s date of first diagnosis/ the control’s date of pseudo-diagnosis on mortality from primary breast cancer. The primary measure of attendance to screening will be whether a woman ever attended at least one screen episode (indicator variable). Secondary measures will be:

• the total number of screens (counts);

• the time since last screen (continuous variable), and whether that time span fell within the past three years (≤ 3 years or > 3 years), as this corresponds to the NHSBSP protocol and approximates the estimated PCDP;

• the time since penultimate screen (continuous or categorical);

• the interval between last screen and penultimate screen (continuous or categorical);

• the maximum interval between 2 screens (continuous or categorical);

• the average interval between 2 screens (continuous or categorical);

• the patient’s age at first screen (continuous or categorical);

• the patient’s age at last screen.

*Ascertainment, self-selection* and *exposure opportunity* biases will be addressed using the methods described in the *Bias & Effect modification* section.

**
*Secondary objectives*
** will consider time since last screen stratified by age at diagnosis/pseudo-diagnosis, by first tumour detection mode, and by region (Main phase only).

The effect of attending a screen in a particular 3-year age band in the main phase (such as 47–49 inclusive), or 5-year age band in the pilot phase, on mortality from primary breast cancer in the subsequent 5-year age band (such as 50–54) will also be investigated, as performed for the cervical screening audit (Sasieni et al., 2009 [22]). The results of this analysis should be very similar to those obtained from the analysis of “time since last screen” after stratifying the analysis by age at diagnosis/pseudo-diagnosis.

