With time since last screen, one might expect an observed increase in incidence (excess risk) immediately after a screen (the screen-detected cases), followed by an observed decrease in incidence (deficit in risk) due to the removal of pre-clinical cases by the screen. The deficit would be expected to be attenuated with time since the screen. The analysis will be stratified by age at diagnosis/pseudo-diagnosis. Indeed, one might expect an excess risk of disease in screened ages (within screening age range) and a deficit in risk in non-screened ages (above screening age range); a potential deficit in risk may also be seen at later ages within the screening age range (i.e. at age 65–69 after up to 15 years of screening). In the absence of overdiagnosis, the initial excess risk from screening would be fully compensated by a deficit in risk over time in the absence of screening (“compensatory drop”, Puliti et al., 2011 [16]). The excess risk in screened ages and the deficit in risk in non-screened ages will be quantified and combined with National Incidence Rates to construct risk scores (Field et al., 2005 [25]) in an attempt to estimate lifetime effect of screening on incidence and overdiagnosis. As the NHSBSP has been running for at least 20 years, there should be sufficient follow-up data after screening stopped (age 70), and the method of “compensatory drop” should achieve full adjustment for lead-time (Puliti et al., 2011 [16]). If the pilot phase of the study highlights little or no follow-up after last screen, lead-time bias will be adjusted using the “postponement of screen-detected cases” method (described in the *Bias & Effect modification* section).

The estimations will be performed for all disease (in situ and invasive) and for invasive disease only.

*Self-selection* and *exposure opportunity* biases will be also addressed using the methods described in the *Bias & Effect modification* section.

**
*Secondary objectives*
** will consider time since last screen stratified by region (Main phase only).

**CC4.** The *primary objective* of this case–control will be to estimate the effect of attendance to breast screening *strictly prior to* date of diagnosis/pseudo-diagnosis on incidence of advanced stage primary breast cancer. The primary and secondary measures of attendance to screening will be as for CC1; in addition, they will include age at last screen.

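### Among ever-screened women, a linear age-at-last-screen term repeats time since last screen with the sign reversed; in other forms it is confounded by recency unless adjusted for it.

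*Protocol article*

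**What the plan says.** Under Statistical methods, the secondary measures for CC1 include "the time since last screen (continuous variable), and whether that time span fell within the past three years" and, as a separate item, age at last screen, for which no functional form is given. CC2 takes over the CC1 measures. CC3a/b also takes them over and then says "in addition, they will include the patient’s age at last screen". CC4 does the same: "in addition, they will include age at last screen". Age at last screen is already in the list that both inherit.

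Three design statements matter:

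- The model: "All case–control study analyses will be conducted using conditional logistic regression. Matching factors (i.e. age, area) are controlled for in the design".
- The birth-date match, given for the general population controls under Participants: selection of cases & controls, with the same tolerance for the diseased controls: "were born within 1 month either side of the case’s date of birth". If no control is found, "the range will be expanded to 3 months either side (or 6 months either side", the wider range applying to cases aged under 50 or over 70.
- The common reference date: under Study design & objectives, the case's diagnosis date is "set as pseudo-diagnosis date in controls".

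The CC1 text remarks that a related analysis, of attending a screen in a given age band, should give results close to those for time since last screen stratified by age. It makes no such remark about age at last screen.

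**The concern.** Conditional logistic regression uses only differences within a matched set. When all members of a set have nearly the same age at the reference date, knowing how long ago a woman was last screened fixes how old she was at that screen. The two listed measures can then carry the same information.

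The protocol expects risk to vary with time since last screen: under CC3a/b it describes an excess just after a screen, then a deficit that fades. If so, an age-at-last-screen analysis can be significant when age at screening has no effect. The Discussion presents the case-control design as having informed cervical screening intervals and age ranges, so an apparent age effect could be misread on a question that matters to a screening programme.

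**Working it through.** The plan states no figure on this point, so there is nothing to reproduce. The check is algebra, then simulation.

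**Algebra.** For woman *j* in set *s*:

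age at last screen = (reference date - date of birth) - time since last screen = A_s + d_j - T_j

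A_s is the case's age at the shared reference date. d_j is the birth-date difference from the case: at most 1 month (0.08 year), or 3 months (0.25 year) or 6 months (0.5 year) after relaxation. A_s is constant within the set and cancels from the conditional likelihood. What remains is d_j - T_j, with d_j small against the spread of T_j.

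**1. Ever-screened women, linear terms.** Simulation of 1400 sets with two controls per case and 23% never screened, the analysis restricted to ever-screened women. Assumptions: age at diagnosis 50-80, risk depending on recency only (log odds 0.08 per year).

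| Birth-date tolerance | Within-set correlation | z, time since last screen | z, age at last screen |
|---|---|---|---|
| exact | -1.0000 | 4.631 | -4.631 |
| 1 month | -0.9998 | 4.497 | -4.462 |
| 3 months | -0.998 | 4.516 | -4.422 |
| 6 months | -0.993 | 2.967 | -2.829 |

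With exact matching the coefficients are 0.0955 and -0.0955 and the log-likelihoods are identical. If both linear terms were fitted together at 1 month, the standard error of the recency coefficient would rise from 0.020 to 1.01, about 50-fold.

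A second simulation of ever-screened women let risk depend only on last screen more than 3 years ago against 3 years or less (300 replicates per cell). With a recency odds ratio of 1.5, the age-at-last-screen test rejected at the nominal 5% level in 59% of runs with 400 sets, 73% with 600, 86% with 800 and 99% with 1400. With no recency effect it rejected in 4-7%.

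**2. Never-screened women kept, with an ever-screened indicator.** The multiplier is now ever-screened times age at last screen. In sets mixing screened and never-screened women, A_s no longer cancels, so the identity fails. Under pure recency of 0.1 per year, mean z was 6.20 for time since last screen and -0.75 for age at last screen (30 runs). With a true screening-by-age interaction and no recency effect, the age term rejected in 70% of runs and the recency term in 37%.

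Confounding remains, and its size depends on the assumed screening histories. In further simulations under pure recency, with 1400 sets and 23% never screened, the linear age term rejected in 23-77% of runs, age bands unadjusted for recency in 13-46%, and bands adjusted for time since last screen in 5-7%. The 23% is 100% minus the 77% coverage quoted in the protocol, used here as an assumed never-screened share.

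**3. Age bands, ever-screened women.** With 3000 sets (before that restriction) and 30 runs per scenario:

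| Truth | Bands alone reject | Bands reject, given linear recency |
|---|---|---|
| recency only | 100% | 10% (3 of 30) |
| age step at 60 (log odds -0.7) | 100% | 97% (29 of 30) |

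Bands can separate an age step because a fixed age cut means different recency in different sets. A cut at 65 is 68 - 65 = 3 years since screening in a set diagnosed at 68, and 72 - 65 = 7 years in a set diagnosed at 72.

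**The case against.** The strongest reply is that the exact equivalence needs choices the article does not make. It does not restrict these analyses to ever-screened women, gives no form for age at last screen, and does not say that both measures enter one model. Those details may belong to a fuller document. Listing several summaries of one screening history is not in itself an error: time since last screen, time since penultimate screen and the interval between them are also linked. Nothing says the age result will be read as independent of recency or used to decide when screening should stop. Recency stratified by age at diagnosis is already planned for CC1, CC3a/b and CC4, so much of the remedy exists.

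Most of this stands, and it limits the point. A reader might infer that every age effect from these sets is spurious, or that an age effect cannot be identified at all. Neither follows. A step in age is detectable in bands adjusted for recency, and a screening-by-age interaction is detectable when never-screened women are kept. A reader might also infer that the plan fits the two terms together and so inflates their variance; it proposes no such model. The identity also does not hold in the sensitivity analysis that extends the controls' pseudo-diagnosis date by up to 4 years, because the reference date is then no longer shared.

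The reply does not remove the confounding. Under each form examined, an age-at-last-screen result unadjusted for recency could exceed its nominal error rate when age at screening had no effect. The protocol lists the measure as an addition without that caution.

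**Conclusion.** The point holds in limited form. Among ever-screened women in these matched sets, a linear age-at-last-screen term adds no usable information beyond time since last screen and should not be read as an age effect. In bands, or with never-screened women retained, the two tests are not the same, but an age result unadjusted for recency is still confounded. Under pure recency with 1400 sets and 23% never screened, that meant 23-77% rejection for the linear term and 13-46% for bands, against a nominal 5%.

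The algebra rests only on the stated matching, reference date and model. The rejection rates rest on assumed screening histories and effect sizes, some on only 30 runs, so they show that the problem can be material rather than predict its size. The primary ever/never analysis and the sample size are unaffected.

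**What to change.** In Statistical methods, for CC1, CC2, CC3a/b and CC4:

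- Do not report linear age at last screen among ever-screened women as a measure separate from time since last screen. State that a linear age effect cannot be separated from recency in these sets.
- Address age in one of two ways. Either use time since last screen by age at diagnosis or pseudo-diagnosis in 5-year bands, with an interaction test; age at diagnosis varies between sets, so this is estimable. Or use bands of age at last screen adjusted for time since last screen.
- If bands are used, say how recency is modelled and how never-screened women enter. Adjusted bands pick up steps or curvature in age; a straight-line age effect would still be absorbed by the recency term.
- Remove the repeated listing under CC3a/b and CC4.

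For CC2, recency by age at diagnosis would have to be added, since its stated stratification is by epoch of diagnosis. No new data are needed. The cost is one fewer stand-alone secondary measure and wider intervals for the adjusted bands.
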